### **9.6.2 Appropriateness of Measurements**

All the efficacy or safety assessments will be standard and consistent with international guidelines.

### **9.6.3 Primary Efficacy Variable**

The primary endpoint used to determine efficacy will be mortality at day 28.

## **9.7. Safety Reporting**

- Adverse events possibly related to study intervention
- SAEs.
- Transfusion related reactions. Transfusion of plasma is procedure with a long-standing experience. The only safety concern with convalescent plasma during acute hospital are transfusion related side effects like transfusion related acute lung injury, serious allergic transfusion reactions and transfusion associated circulatory overload.

### 9.7.1 Definitions

- An adverse event (AE) is any new, undesirable medical experience or change of an existing condition which occurs during or after treatment, whether considered related to the treatment received. Adverse events will be graded according to the NCI Common Terminology Criteria for Adverse Events (CTCAE) v4.03 as: 1=mild, 2=moderate, 3=severe, 4=life threatening, and 5=fatal. Relatedness to the plasma therapy will be scored as follows: 1=not related, 2=unlikely related, 3=possibly related, 4=probably related and 5=definitely related.
- A serious adverse event (SAE) is any experience with a significant hazard and includes any event that:
  - is fatal
  - is life-threatening (places the patient at immediate risk of death)
  - requires or prolongs hospitalization
  - is permanently or significantly disabling/incapably
  - is a (new) malignancy
  - is a congenital anomaly/birth defect
  - is a known or suspected overdose

### 9.7.2 Safety reporting procedures

AEs at least possibly related to the plasma infused are to be reported in the CRF.

Any AE should be documented and followed until it is resolved. New AE appearing after the start of a subsequent disease treatment that is not part of this protocol should not be reported anymore.

Adverse events (as specified above) and Serious adverse events must be reported from the initiation of treatment until day 28 after treatment, excepted death that has to be reported until the primary endpoint is reached.

SAEs must be recorded on the Serious Adverse Event Report form, and reported by e-mail to sponsor within one working day (24 hours) of discovery. The local investigator is responsible for transmission to the Principal Investigator and to the chair of the DSMB.

## 9.8. Confidentiality and data handling

- Data will be collected at each center on the eCRF. The investigator of each participating center will be responsible for entering these data into the central database with the help of a clinical research assistant. All statistical analyses will be performed centrally in Liège.
- Patient data will remain confidential, but paper and/or electronic medical records may be reviewed for trial purposes by authorized individuals other than the treating physicians that are involved in the conduct of the trial. All patients are assigned a unique patient number. This number will be used in any publication that describes the research that the patient has participated in, thereby preventing identification of the patient. All research records are maintained in a locked room, and access to electronic files are restricted by a password. Data protection according to the EU General Data Protection Regulation (2016/79 of April 27th, 2016) is described in details in each site agreement (Data protection agreement)

## 9.9. Statistical Analysis

- Primary outcome

The primary outcome of the trial is mortality at day 28. Based on prior reports from China, Italy and UK, and consistent with personal observations, we anticipate that the mortality at day 28 will be around 40 %. As no comparative study has yet been published, the reduction that we anticipate is empiric. We consider that a one third relative reduction in 28-day mortality is realistic and clinically relevant. As this reduction might be greater, we plan to perform an interim analysis for ethical reasons. With a two-sided  $\alpha$ -risk of 0.05 and a  $\beta$ -risk of 0.20, the minimal number of patients to include to reach significance for a one third relative reduction in 28-day mortality (an absolute reduction of 13.5% day-28 mortality in the intervention group assuming a day-28 mortality of 40 % in the control group) is 250 in the control group and 250 in the active group (total number of patients = 500). This number allows for four interim analyses to be performed in addition to the final analysis, respectively after assessment of 100, 200, 300, 400 and 500 patients. Considering that others trials in COVID-19 may result in modification in mortality and therefore in standard of care, we anticipate that the number of patients that is necessary to address our hypothesis may vary, and will have to be adapted depending on the results of the interim analyses.

- Statistical analysis plan

Results will be analysed in intention to treat and expressed as means and standard deviations (SD) for quantitative variables with a Normal distribution and as medians and 25th to 75th percentiles for skewed distributed quantitative variables. Qualitative variables will be expressed using counts and percentages.

Mean values between groups will be compared by Student t-test but also by the non-parametric Wilcoxon test when normality assumption is not fulfilled. Proportions will be compared by the chi-square

test. Appropriate multivariate analyses will be performed to assess the relationship between outcome and patients' characteristics and clinical features.

For the primary endpoints, vital status at day 28 in all groups will be calculated with corresponding 95% CI. Comparison between groups will be tested using chi-square test.

Regarding the secondary endpoints, quantitative values between groups will be compared by Student t-test or non-parametric Wilcoxon for the SOFA score (at different time points), viral load of SARS-CoV-2 (at different time points), circulating CRP (at different time points), ADL score at day 90, anxiety-depression scale at day 90, sero-conversion. Poisson regression analysis will be considered to analyse number of ventilator-free days up to day 28. Comparison of proportions will be applied to compare location of patient at day 90, as well as presence of various adverse events. If descriptive analysis revealed the presence of potential confounding factors, appropriate multivariate analysis will then be considered.

The two-sided level of significance used in this trial is 5%. Statistical analyses will be carried out using SAS (version 9.4 for Windows) statistical package.

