| 
Procedures: Visits at days 7, 21, 14, 28, 90 and 365.
                                                                                                                                                                                                                                                                                                                                                                                                                                                                                                                                                                                                                |
| 
Duration of treatment = 2 hours, duration of surveillance per patient = 365 days
                                                                                                                                                                                                                                                                                                                                                                                                                                                                                                                                                                                     |
| 
Statistical Considerations: Intention to treat analysis, expected mortality at day 28 = 40%, expected relative reduction with study intervention = 30 %, <math>\alpha</math> = 5%, <math>\beta</math> = 20%, number of subject to include = 500. Interim analyses at 100, 200, 300 and 400 patients included.
                                                                                                                                                                                                                                                                                                                                                        |

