### **9.5.3 Process of randomization**

The process of randomization will be performed through a standard randomization system (UCL clinical trial center, Pr [name]) either directly through the eCRF system or by the CCC St Luc. The randomization process will be stratified according to the delay from tracheal intubation to inclusion (" $\leq$  48 hours"; "between 48 hours and 5 days"). A response to telephone calls for any issue regarding the inclusion criteria will be available 24/7 (see "availability of the study product" paragraph).

The treatment (intervention versus control) will be allocated in 2 arms in a 1:1 ratio. The randomization table will be made of permuted block size provided by the statistician.

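### Randomisation is stratified by intubation delay but the primary chi-square test ignores the stratum: valid, conservative if delay is prognostic, and free to improve

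*Protocol*

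**What the plan says.** On allocation, Protocol Section 9.5.3 states: "The randomization process will be stratified according to the delay from tracheal intubation to inclusion". The two levels are up to 48 hours, and 48 hours to 5 days. Arms are allocated 1:1 in permuted blocks. No reason is given for choosing this factor.

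On the primary endpoint, the paragraph of Section 9.9 on vital status at day 28 asks for the mortality in each group with a 95% CI and then says "Comparison between groups will be tested using chi-square test". Neither the stratum nor any covariate is named there. The interim analysis plan in the same section does not name the stratum either.

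On adjustment, Section 9.9 contains two statements. One promises, without condition, multivariate analyses relating outcome to patient characteristics; it names no covariate or model. The other closes the paragraph on secondary endpoints: "If descriptive analysis revealed the presence of potential confounding factors, appropriate multivariate analysis will then be considered".

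The trial is open label (Section 9.4.4).

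**The concern.** Stratified allocation balances the arms on delay. If delay is related to mortality, the difference in death rates then varies less from trial to trial than the ordinary chi-square formula assumes. The test uses a standard error that is too large. It rejects less often than its nominal level under the null, gives a CI that is somewhat too wide, and loses power that the randomisation has already paid for.

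The conditional sentence is a separate and smaller matter. In a randomised trial, differences seen in baseline tables are chance, so they are a poor guide to which covariates to adjust for. With allocation visible and no covariates named, an adjusted result can be challenged as selected after the fact.

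**Working it through.** **Inputs from the protocol**

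- Two-sided alpha 0.05 ("The two-sided level of significance used in this trial is 5"%) and power 0.80 (beta: "risk of 0.20, the minimal number of patients to include to reach significance"), Section 9.9.
- Control mortality 40% ("assuming a day-28 mortality of 40 % in the control group"), Section 9.9.
- Effect: "an absolute reduction of 13.5% day-28 mortality in the intervention group" in Section 9.9 (40% vs 26.5%). The synopsis has "expected relative reduction with study intervention = 30"% (40% vs 28%). Both are used below.
- 250 per arm, 1:1, two delay strata.

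**Inputs not in the protocol (assumed)**

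- Equal strata, averaging 40% mortality.
- A mortality gap between strata of 0 to 30 points. Section 8 quotes 30% and 70% survival for early and late ventilation, but that concerns timing in the course of the disease. It is not delay from intubation to inclusion, so it cannot serve as an estimate here.

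**Step 1: reproduce the sample size.** For a fixed design,

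n per arm = [1.96·√(2p̄(1−p̄)) + 0.84·√(p₁(1−p₁) + p₂(1−p₂))]² / (p₁−p₂)²

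This gives 190 per arm for 40% vs 26.5% and 244 for 40% vs 28%. With 250 per arm and a single look, power is 89.6% and 81.0%. Applying Table 2's efficacy and futility thresholds at each look (400,000 simulated trials) gives 78.6% at 26.5%. So 500 patients is consistent with a sequential design of about 80% power, and 80% is a fair base.

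**Step 2: effect of ignoring the stratum.** Let r be the ratio of within-stratum to total variance:

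r = ½[p_L(1−p_L) + p_H(1−p_H)] / (0.40 × 0.60)

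At 80% power the expected test statistic is 1.96 + 0.84 = 2.80. Under stratified allocation the unstratified statistic has standard deviation √r instead of 1. The stratified statistic has mean 2.80/√r and standard deviation 1. Hence:

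- type I error, unstratified: 2[1 − Φ(1.96/√r)]
- power, unstratified: Φ((2.80 − 1.96)/√r)
- power, stratified: Φ(2.80/√r − 1.96)

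Worked case, strata at 30% and 50%: r = ½(0.21 + 0.25)/0.24 = 0.958 and √r = 0.979. Type I error: 1.96/0.979 = 2.002, giving 4.5%. Unstratified power: 0.84/0.979 = 0.858, giving 80.5%. Stratified power: 2.80/0.979 − 1.96 = 0.900, giving 81.6%.

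| Stratum mortality | r | Type I, chi-square | Power, chi-square | Power, stratified | Gain (points) |
|---|---|---|---|---|---|
| 40% / 40% | 1.000 | 5.0% | 80.0% | 80.0% | 0 |
| 35% / 45% | 0.990 | 4.9% | 80.1% | 80.4% | 0.3 |
| 30% / 50% | 0.958 | 4.5% | 80.5% | 81.6% | 1.1 |
| 25% / 55% | 0.906 | 4.0% | 81.1% | 83.7% | 2.6 |

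The comparator is the chi-square test's own power under stratified allocation, not a nominal 80%. Using 80% would overstate the last two gains as 1.6 and 3.7.

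**Step 3: check by simulation.** At 40% vs 26.5%, 500 patients, a single look at 0.05 and 100,000 trials per case, chi-square against Cochran-Mantel-Haenszel (CMH) gave 89.8% vs 89.8%, 90.1% vs 90.5% and 90.9% vs 92.0% for gaps of 10, 20 and 30 points. Type I error was 4.7%, 4.6% and 4.0% for chi-square, and 4.8% to 5.1% for CMH. The gains are smaller here because power is already near 90%. With 70% of patients in one stratum, the gain for gaps up to 30 points was at most 0.8 points.

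With Table 2's thresholds, the 28% effect and no stopping for futility (200,000 trials), CMH raised power from 80.8% to 82.1% (20-point gap) and from 81.3% to 84.2% (30-point gap). If the futility rules were followed, the gains were 0.6 and 1.4 points.

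**Step 4: data-driven adjustment.** Assumptions: no treatment effect, five binary covariates each with odds ratio 2, 250 per arm, 20,000 trials. Adjusting mechanically for whatever looked imbalanced gave type I error of 4.3% to 4.6%. Freedom to report the best of the unadjusted, triggered and fully adjusted results gave 6.7% to 6.8%. The risk therefore comes from freedom to choose between results, not from adjustment itself.

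**The case against.** The strongest reply is that a pre-specified unadjusted chi-square after stratified randomisation is a legitimate test. Its error rate is at or below 5%, mortality is an objective endpoint, and test options and covariate lists usually belong in a statistical analysis plan, which is not shown here. CMH is itself a chi-square statistic, so the sentence might only be terse. Much of this stands: nothing here threatens validity, and the gain is modest. What remains is that the protocol names both the stratification factor and the primary test, and nowhere joins them. That is a choice written into the protocol, and it can be improved there.

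A reader might also infer three stronger things that the protocol does not support.

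- That adjustment occurs only if the data prompt it. Section 9.9 also promises unconditional multivariate analyses, and the conditional sentence sits with the secondary endpoints; whether it reaches the primary endpoint is unclear.
- That the sponsor stratified because it expects delay to predict death. Section 9.5.3 gives no reason.
- That the primary test forgoes power worth 11% to 25% more patients. That figure needs age and SOFA in the primary test and an assumed 10% to 20% of outcome variance explained (1/0.9 = 1.11; 1/0.8 = 1.25). The protocol has no such figure, and the change recommended here keeps those covariates in a supportive model.

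**Conclusion.** The point holds as a modest and free improvement. The primary test does not use the factor by which patients are randomised. It stays valid, and is conservative to the extent that delay is prognostic. With equal strata and a gap of 10 to 30 points, type I error is about 4.9% to 4.0% in place of 5%, and the stratified test gains about 0.3 to 2.6 power points from an 80% base. At the 13.5-point effect with a single look the gain is about 0 to 1.1 points. If delay is unrelated to mortality it is nil. These sizes rest on assumed stratum mortality and stratum shares, since the protocol gives neither.

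The conditional adjustment sentence is a lesser fault, confined on its face to the secondary endpoints. It leaves the covariates open until the data have been seen in an open-label trial.

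**What to change.** In Section 9.9, make the primary comparison a CMH test stratified by the two delay levels, reported with a stratified risk difference and its 95% CI, and use the same test at the interim and final looks. Table 2's P-value thresholds can be applied to it directly.

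Replace the conditional sentence with one pre-specified supportive analysis adjusted for delay stratum, age and baseline SOFA, with no covariate chosen from observed differences between arms. State which endpoints it covers.

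The cost is two sentences. The stratum is held in the randomisation system, and date of birth and SOFA are already recorded at the inclusion visit (Section 9.5.4.2). Sample size and alpha do not change.

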### 7.3. Endpoints

The principal endpoint will be vital status (dead/alive) at day 28

The secondary endpoints will be

- day-90 mortality
- number of ventilator-free days at day 28
- number of renal replacement therapy-free days at day 28
- number of vasopressors-free days at day 28
- use of ECMO before day 28
- value of the SOFA score at days 7, 14 and 28 [1] (see appendix A).
- changes in SOFA scores over the following 7, 14 and 28 days
- value of the SARS-CoV-2 viral load, expressed as cycle threshold, [2] in the tracheal aspirates (for intubated patients) or nasopharyngeal swabs (for extubated patients) at days 7, 14 and 28
- blood C reactive protein (CRP) concentrations at days 7, 14 and 28
- length of stay in the acute care hospital
- location of the patients at day 90: acute care hospital, post-acute care hospital, long-term residency, home
- WHO progression scale prior transfusion, at day 7 and at discharge (see appendix B)
- Hospital Activity of Daily Living (ADL) functional score at day 90 and at day 365. [3] (see appendix C).
- Anxiety-depression evaluation scale at day 90 and at day 365. [4] (see appendix D ).
- Quality of life scale (EQ-5D-5L) at day 90 and at day 365. [5] (see appendix E).
- Transfusion-related adverse events within 7 days
- Sero-positivity to SARS-CoV-2 at days 1, 7, 28 and 90
- Adverse events related to standard of care (mechanical ventilation, prolonged decubitus, prone positioning...) such as:
  - o Ventilator associated pneumonia
  - o Secondary bacteremia [6]
  - o Deep vein thrombosis and pulmonary embolism
  - o Pressure ulcers, stage 2 to 4 (*i.e.* loss of skin, of tissue or of bone) [7]
  - o Ventilator induced baro-traumatism (pneumothorax, pneumo-mediastinum, sub-cutaneous emphysema) [8]
  - o Accidental ablation of tracheal or vascular device [9]
  - o Ventilator induced baro-traumatism (pneumothorax, pneumo-mediastinum, sub-cutaneous emphysema) [8]
  - o Accidental ablation of tracheal or vascular device [9]

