#### **9.5.4.2 Inclusion visit (Day 1)**

Parameters will be obtained as part of the routine clinical care. They will include

- Date of Birth
- Male/Female
- Weight kg
- Height cm
- Clinical frailty scale (appendix F)
- ADL (estimated before COVID-19)
- EQ-5D-5L (estimated before COVID-19)
- marital status
- highest diploma
- work situation
- Reference serum creatinine

Comorbidities (yes/no)

- Hypertension
- Coronary heart disease
- Congestive heart failures

- Chronic obstructive pulmonary diseases
- Asthma
- Fibrotic pulmonary disease
- Neurological disease
- Connective tissue disease
- Diabetes
- Chronic renal failure
- Cirrhosis
- Active solid cancer without metastases
- Active solid cancer with metastases
- Haematological cancer
- AIDS/HIV

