#### Clinical findings

- APACHE II score calculation, based on the following criteria
- SOFA score calculation, based on the following criteria
- Glasgow coma score
- Systolic arterial pressure
- Mean arterial pressure
- Need of vasopressor
- Need of ECMO
- PEEP
- Pplat
- Prone positioning

- 24 h diuresis
- Need of renal replacement therapy
- Highest temperature

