## **9.6. Efficacy and Safety Variables**

### **9.6.1 Efficacy and Safety Measurements Assessed and Flow chart**

Measurements will be performed by the investigators and clinical research assistants during their stay in the hospital and during medical visits at each time of endpoints (days 7, 14, 28, 90) in case of hospital discharge, and by phone for day 365 endpoint.

Vital status, dependence on the ventilator and clinical and biological data to calculate the SOFA score will be collected from the patient's record. Viral load, expressed as cycle threshold, will be assessed from tracheal aspirates or naso-pharyngeal swabs and RT-PCR assessment by the usual technique of the routine laboratory. Adverse events possibly related to study intervention will be collected prospectively, according to definitions of iatrogenic events, transfusion-related events and nosocomial infections by the investigator and the clinical research assistant in charge of the study. Scales assessing functional state, psychological state and quality of life will be collected at day 90 visit and over the phone at day 365 visit by a clinical research assistant dedicated to this task by the coordinating center. The adverse events will be collected and severity rating according to Belgian guidelines.

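### SOFA, CRP, viral load and day-90 ADL get unadjusted two-sample tests although baseline values and the stratum are collected, and SOFA and ADL have no value for patients who die

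*Protocol*

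**What the plan says.** All references are to the protocol.

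- **Tests.** Section 9.9 fixes the comparison: "quantitative values between groups will be compared by Student t-test or non-parametric Wilcoxon for the SOFA score (at different time points"), followed in the same list by "viral load of SARS-CoV-2 (at different time points), circulating CRP (at different time points), ADL score at day 90". No covariate is named.
- **Adjustment.** Section 9.9 makes a general statement, "Appropriate multivariate analyses will be performed to assess the relationship between outcome and" patient features, and for the secondary endpoints a conditional one: "If descriptive analysis revealed the presence of potential confounding factors, appropriate multivariate analysis will then be considered".
- **Baseline data.** The inclusion visit (9.5.4.2) lists "SOFA score calculation, based on the following criteria" and "ADL (estimated before COVID-19"). CRP is among the day-1 laboratory values. Viral load is marked for day 1 in the flow chart but is absent from the inclusion-visit list.
- **Change score.** Section 7.3 lists "changes in SOFA scores over the following 7, 14 and 28 days" as a separate secondary endpoint.
- **Stratum.** Section 9.5.3 stratifies randomisation by time from intubation to inclusion (up to 48 hours, or 48 hours to 5 days).
- **Ct values.** Section 9.6.1 has viral load measured by "RT-PCR assessment by the usual technique of the routine laboratory"; the synopsis gives 16 centres.
- **Death.** Section 9.9 says intention to treat and gives no rule for a score that is absent because the patient died. SOFA (Appendix A) and the ADL index (Appendix C, 0 to 6) have no level for death. The WHO progression scale (Appendix B) does: death scores 10.

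**The concern.** Two things are at stake.

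The first is precision. In a randomised trial, the day-1 value of a continuous outcome is usually its best single predictor, and adjusting for it costs nothing once it has been collected. A raw comparison discards that information. Tying adjustment to what the descriptive tables show is worse than naming covariates in advance. The treatment is open label, and a choice of covariates made after seeing the data can move the result either way.

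The second is interpretation. A t-test or Wilcoxon test needs a number for each patient. With mortality near 40% in controls, a large share of patients will have no day-28 SOFA or day-90 ADL unless a rule supplies one. The missing share differs between arms if the trial succeeds. The test then compares groups selected by the outcome that plasma is meant to change.

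**Working it through.** The plan states no variance or power for these endpoints, so there is no figure of its own to reproduce. The inputs taken from it are 250 patients per arm, 40% control mortality at day 28, and an absolute reduction of 13.5 points (40 − 13.5 = 26.5%), all from section 9.9. The correlations below are assumptions; the documents give none.

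**1. Precision.** With equal variances at baseline and follow-up and baseline correlation r, the variance relative to a raw follow-up comparison is 1 − r² for ANCOVA and 2(1 − r) for a change score.

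| r (assumed) | Raw | Change score | ANCOVA | ANCOVA patients equivalent to 500 raw |
|---|---|---|---|---|
| 0.3 | 1 | 1.40 | 0.91 | 455 |
| 0.5 | 1 | 1.00 | 0.75 | 375 |
| 0.7 | 1 | 0.60 | 0.51 | 255 |

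ANCOVA therefore reduces variance by 9%, 25% or 51%. Against the change score its ratio is (1 − r²) / [2(1 − r)] = (1 + r)/2, that is 0.65, 0.75 and 0.85. Delta SOFA uses the day-1 value, but less efficiently than ANCOVA at every r below 1. For r below 0.5 it is noisier than the raw value.

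**2. Who has a day-28 value.** Control: 250 × 0.60 = 150. Plasma: 250 × 0.735 = 183.75, about 184. About 100 control and 66 plasma patients have none. With the synopsis's 30% relative reduction (40% to 28%), plasma survivors number 250 × 0.72 = 180.

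**3. Shift if plasma only prevents deaths.** Let death occur when a standard normal severity exceeds a threshold, and let the score correlate rho with severity. The mean severity of survivors is −φ(t)/Φ(t), where Φ(t) is the survival proportion:

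- control, survival 0.60: −0.644
- plasma, survival 0.735: −0.446
- difference: 0.198 SD, multiplied by rho for the score.

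The chance of a significant result against plasma is 1 − Φ(1.96 − z), with z the shift over its standard error for 150 and 184 survivors. At rho = 0.5 the shift is 0.099, the standard error about 0.102 and z = 0.97, giving 16%.

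| rho (assumed) | Shift against plasma, SD | Chance of a significant result against plasma (2.5% if no shift) |
|---|---|---|
| 0.3 | 0.06 | 8% |
| 0.5 | 0.10 | 16% |
| 0.7 | 0.14 | 31% |

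At 28% plasma mortality the shifts are 0.05, 0.09 and 0.12 SD.

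**4. Other mechanism and remedies.** These come from simulation: 2,000 runs, 250 per arm, 40% versus 26.5% mortality, assumed correlation of 0.5 between baseline and severity, and rho = 0.3 / 0.5 / 0.7.

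- If plasma lowers severity itself, the survivor comparison favours plasma by 0.06 / 0.09 / 0.12 SD, with power of only 8% / 14% / 25%.
- If plasma only prevents deaths, baseline adjustment among survivors reduces the shift only from 0.058 to 0.050, 0.097 to 0.083 and 0.138 to 0.118 SD.
- A Wilcoxon test on all randomised patients with death ranked worst favours plasma in 68% / 58% / 47% of runs if plasma only prevents deaths, and in 84% / 88% / 92% if it lowers severity. No run was significant against plasma.

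**The case against.** Three stronger readings are tempting, and the protocol supports none of them.

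- **That the plan ignores the day-1 values.** It does not do so for SOFA: the change in SOFA is a listed endpoint. Two sentences in section 9.9 also allow multivariate analysis. What remains is that no baseline value is named as a covariate and that adjustment of the secondary endpoints is conditional on the data.
- **That the plan excludes the dead.** No sentence says so. Section 9.9 says intention to treat, and a rule for values truncated by death is commonly left to the statistical analysis plan, which is not at hand. A survivor-only comparison is what the named tests would give in practice on scales without a death level; it is not a stated rule.
- **That the results are biased against plasma.** The figures in step 3 require plasma to prevent deaths without changing the score. The stated hypothesis is that plasma also alleviates symptoms and lowers viral load, and then the survivor difference favours plasma. The correlation rho is unknown.

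Other parts of the objection also stand. Omitting a covariate does not bias a randomised comparison; it only costs precision, by an amount the documents do not fix. The ADL baseline is a retrospective pre-COVID estimate and may predict day 90 weakly. The survivor counts are for day 28 and do not carry over to days 7, 14 or 90. A death-ranked analysis answers a different question: it can favour plasma on SOFA when only deaths differ, and mortality is already analysed separately. It cannot simply replace the survivor comparison.

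**Conclusion.** The point holds in limited form. Section 9.9 commits to unadjusted tests for four secondary outcomes while the baseline values and the stratum are collected, and it makes adjustment depend on what the data show. Pre-specified ANCOVA is the better method at no cost in data. The variance saving is 9% to 51% for an assumed baseline correlation of 0.3 to 0.7, and may be small for ADL.

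The survivor problem is a risk rather than a demonstrated bias. Its size (0.06 to 0.14 SD at day 28) rests on the planned mortality, an assumed rho of 0.3 to 0.7 and a mechanism in which plasma only prevents deaths. The direction of the observed difference depends on that mechanism. Baseline adjustment removes little of the shift, so the two weaknesses need separate remedies. The primary endpoint, the sample size and the interim rules are unaffected.

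**What to change.** 1. For SOFA, CRP and Ct, pre-specify ANCOVA (or rank ANCOVA where distributions are skewed) with the day-1 value and the intubation-delay stratum. For Ct, add laboratory or centre. Do not adjust for specimen type, because it depends on extubation after randomisation.
2. For day-90 ADL, use the pre-COVID estimate and the stratum, accepting that the gain may be small.
3. Remove the data-driven adjustment clause for these endpoints.
4. Add day-1 viral load to the inclusion-visit list so that it agrees with the flow chart.
5. For SOFA and ADL, report a rank analysis of all randomised patients with death ranked worst beside the survivor-only comparison, and label the survivor-only results descriptive.

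The cost is wording in the protocol or statistical analysis plan; the flow chart already plans the measurements. The drawback of item 5 is that death-inclusive ranks mix mortality with organ function or independence, which is why both results should be shown.
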